### Statistical analysis

All analyses is detailed in a statistical analysis plan. Patients from each cohort will be analyzed separately on an intent-to-treat basis. Descriptive statistics will be provided for all discrete variables in the form of rates and proportions with 95% confidence intervals (CI). Continuous variables will be escribed by mean, standard deviation, median and range. Overall survival, disease-free survival, local recurrence rate and metastasis rate will be estimated using the method of Kaplan Meier. Exploratory comparisons of discrete variables will be performed using a Chi-squared test, using continuity correction or Fisher’s exact test. Continuous variables will be compared using a Student’s t-test, or a non-parametric equivalent (Wilcoxon). Survival statistics will be based on a stratified log-rank test. All tests will be two sided with a *p*-value of less than 0.05 considered to indicate statistical significance.

An interim analysis is planned after having recruited 300 patients, 75 patients at least per cohort, in order to evaluate whether a success rate around 85% is achieved for each cohort; a lower limit of 75% is not acceptable, for which reason the data from the treatment groups with a success rate < 75% will be excluded from further analysis. None a priori expectations of differences can be made based in current literature.

A propensity score will be constructed as the individual prediction (in logit scale) of a logistic regression model in which the outcome is modeled with different potential confounding factors. The propensity score will be added as a continuous variable to adjust the risk models. The Generalized Linear Model (GLM) approach allows for the construction of multilevel and mixed models, which will be useful for controlling the inter-hospital random variability.

Secondary end-points will be analysed according to their characteristics: GLM with identity link will be used for operative time, number of harvested lymph nodes and length of stay, GLM with logit link will be used for unplanned conversion, complete mesocolic excision and R0 resection and Cox regression will be used for middle-term oncologic results: overall survival, disease-free survival, local recurrence and metastasis.

Patients with missing data in planned surgical approach will be be excluded from the study. Patients with missing data in any end-point will be excluded from the analyses on that end-point, and patients with missing data in variables included in the propensity score will have their data imputed using multiple imputation procedures.

Three sensitivity analyses will be used for the primary end-points. The analysis will be repeated k times omitting a hospital each time (k = number of participant hospitals). In addition to intention-to-treat analysis, a sensitivity analysis will be conducted excluding patients with conversion. The analysis will be repeated stratifying by tertiles of the propensity score.

Stata/SE software will be used to perform the statistical analysis (versions 14–16 [forthcoming]).

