## Methods/design

### Patient recruitment

Patients included in the study will be adults (male or female aged ≥18 years) with a benign or malignant tumor in the right colon that require an elective right colectomy with curative intent. Patients will have a life expectancy of at least 12 weeks, with an adequate performance status (Eastern Cooperative Oncology Group Scale score ≤ 2). All patients will have voluntarily signed and dated an Ethics Committee-approved informed consent form before inclusion, obtained by the investigator or designee. Patients will be excluded if they have cT4b tumors, metastatic disease, planned colonic surgery along with other major concomitant procedures (e.g. liver resections, other intestinal resections), or have inflammatory bowel disease (i.e. Crohn’s disease or ulcerative colitis). Patients who are pregnant or suspected to be pregnant, have a comorbid illness or condition that would preclude the use of surgery, are undergoing emergency procedures, or are unwilling to comply with all follow-up study requirements will also be excluded. All patients will be screened and recorded during enrolment to identify any selection bias, which can be higher in observational studies [6].

Eligible patients will be recruited from the approved participating centers according to the surgeons’ experience with each technique. It is calculated that at least 1200 patients (300 per cohort) should be enrolled in the study. The assumptions for the sample size were based on the incidence of surgical wound infection and Clavien-Dindo grade > IIIa complications. The sample size is based on attaining a success rate of 85% for the primary endpoint, with the lower 95% confidence limit being no greater than 5% from the estimated success rate. Assuming a 2-sided interval, a total of 245–317 patients will be required within each cohort. Accounting for a 10% loss to follow-up, a total of 1200 patients will be recruited so that the four parallel cohorts will have sufficient power to make multiple comparisons.

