### Outcomes

The efficacy of the surgical method will be defined as the lack of surgical wound complications (infection, hematoma, hernia as late complication of wound infection…) and reduced severe complications. The primary composite endpoint will comprise two measures of success: Having either a surgical wound infection or a Clavien IIIb-IV postoperative complication constitute the primary composite endpoint. This means, that a patient having either a surgical wound infection or a Clavien IIIb-IV [10] complication would be scored as a “1”. Surgical wound infection will be assessed at the 30 postoperative day visit using specific wound assessment questions (purulent drainage, positive wound cultures, wound opened to drain and classical flogotic signs). These questions are recorded at the eCRF (Yes recorded as 1, No recorded as 0). In all cohorts, secondary endpoints will include oncologic results at 2 years, overall survival, disease-free survival, local recurrence, metastases rate, rate of unplanned conversions to open surgery, operative time (min), complete mesocolic excision, number of harvested lymph nodes, R0 resection, length of stay (days), ventral hernia (assessed 1 and 2 years after the right colectomy), patient-assessed quality of life measures (the European Organization for Research and Treatment of Cancer Quality of Life Questionnaires C30 and CR29), and systemic inflammatory response syndrome (C-reactive protein, with optional procalcitonin). Optional measures, to enable a medico-economic sub-study, include EQ-5D, time to ambulation, patient return to work/activity, pain evaluation, and resource utilization for procedure and follow-up care.

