**Fig. 2 Fig2:**
[figure not shown]
Study assessments. BMI, body mass index; CME, complete mesocolic excision; CT, computed tomography; ECA, extracorporeal anastomosis; ERAS, enhanced recovery after surgery; EORTC, European Organization for Research and Treatment of Cancer; ICA, intracorporeal anastomosis; PET, positron emission tomography; QLQ-C, quality of life questionnaire for cancer patients; QLQ-CR, quality of life questionnaire for colorectal cancer patients

**Table 1 Tab1:** Assessment schedule

	Baseline	Procedure	Discharge	30 days ±7 days	90 days ±14 days	1 year ±30 days	2 years ±30 days	Unscheduled visit
Informed consent	X							
Demographics and medical history	X							
Procedure details		X						
SIRS (CRP) *Optional: PCT*		X						
Pathology				X				
CT scan/PET scan^c^	X					X	X	
Complications		X^a^	X^a^	X^a^	X^a^	X^a^	X^a^	X^a^
Quality of life: EQOL	X				X	X		
Study exit forms							X^b^	

^a^Complete if applicable; ^b^complete when lost to follow-up, consent withdrawal or subject has completed all study related visits; ^c^CT scan results will be collected if done per the sites standard protocol: every 6 months for malignant disease; after at least 1 year to assess hernia in benign disease. *CRP* C-reactive protein (collected at days 1 and 3 postoperative); *CT* computerized tomography, *PCT* procalcitonin (optional, collected at days 1, 3, 5 postoperative); *PET* positron emission tomography, *SIRS* systemic inflammatory response syndrome

Primary data collection will be performed by a study coordinator or designee. The data will be collected on the electronic case report forms (CRF), hosted in a study-specific, dedicated electronic data collection (EDC) system. The database has been developed and utilized in accordance with international requirements and standards applicable to clinical investigations i.e. good clinical practice (GCP) and is a GCP-compliant environment meeting applicable 21 CFR Part 11 requirements. A copy of the completed CRF will remain on site at the participating center at the end of the study. All data requested on the CRFs will be recorded. All missing data will be explained. The European Society of Coloproctology will conduct two independent snapshot audits during the study, during the first and second years, which will also collect information on all right colectomies performed in the participating institutions.

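### Kaplan-Meier is named for local recurrence and metastasis although death is a competing event, and these endpoints are not limited to malignant tumours

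*Protocol article*

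**What the plan says.** The Statistical analysis section puts four endpoints under one estimator: "Overall survival, disease-free survival, local recurrence rate and metastasis rate will be estimated using the method of Kaplan Meier". For comparisons it adds "Survival statistics will be based on a stratified log-rank test" and "Cox regression will be used for middle-term oncologic results: overall survival, disease-free survival, local recurrence and metastasis". No competing-risk method is named, and the handling of death in the recurrence and metastasis analyses is not described.

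On the population, Patient recruitment admits adults "with a benign or malignant tumor in the right colon". The Outcomes section says: "In all cohorts, secondary endpoints will include oncologic results at 2 years, overall survival, disease-free survival, local recurrence, metastases rate". The Statistical analysis section analyses each cohort by intention to treat, and its exclusions concern missing data, not histology. Only the imaging schedule separates the two groups: footnote c of Table 1 has CT results collected, where done under the site's standard protocol, "every 6 months for malignant disease; after at least 1 year to assess hernia in benign disease".

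The article refers the detail of all analyses to a statistical analysis plan (SAP), which was not available for this review.

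**The concern.** Two features of the stated method affect how the 2-year oncologic rates can be read.

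**Competing death.** Kaplan-Meier treats a censored patient as still able to have the event later. A patient who has died without recurrence cannot. If deaths are censored, one minus Kaplan-Meier estimates the recurrence risk in a hypothetical setting without death. It exceeds the proportion of patients who actually recur.

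**Benign tumours.** A patient with a benign tumour is taken to have no risk of cancer recurrence or metastasis and would add only event-free follow-up. A pooled rate then depends on the cohort's benign share. That share can differ between techniques, because patients enter a cohort through their surgeon. At the planned 30 patients per surgeon and 300 per cohort, about 300/30 = 10 surgeons determine each cohort's case-mix.

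At stake are secondary results that the abstract lists among the mid-term outcomes of the study.

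**Working it through.** **Inputs.** The article gives no 2-year recurrence, metastasis or mortality rate and no expected benign share. There is therefore no stated figure to reproduce, and every rate below is an assumption. The 2-year horizon and the 300 patients per cohort are from the article.

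**Step 1: competing death.** Assume constant hazards. Let r be the 2-year value of one minus Kaplan-Meier with deaths censored, and d the corresponding 2-year probability of death without recurrence.

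- λ1 = −ln(1 − r)/2 and λ2 = −ln(1 − d)/2
- Cumulative incidence = λ1/(λ1 + λ2) × [1 − exp(−2(λ1 + λ2))] = λ1/(λ1 + λ2) × [1 − (1 − r)(1 − d)]

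With r = d = 10%, λ1 = λ2, so cumulative incidence = 0.5 × (1 − 0.90 × 0.90) = 0.5 × 0.19 = 9.5%. Kaplan-Meier would show 10%.

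| 1 − KM (r) | Death (d) | Cumulative incidence | Excess, points | Relative excess |
|---|---|---|---|---|
| 3% | 3% | 2.96% | 0.04 | 1.5% |
| 5% | 5% | 4.88% | 0.12 | 2.6% |
| 10% | 5% | 9.75% | 0.25 | 2.5% |
| 10% | 10% | 9.50% | 0.50 | 5.3% |
| 10% | 15% | 9.24% | 0.76 | 8.2% |
| 15% | 15% | 13.88% | 1.12 | 8.1% |

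With both inputs ranging over 3–15%, the excess is 0.04 to 1.12 points, or about 1.5–8% relative. The relative excess is driven almost entirely by mortality.

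**Step 2: benign share.** Assume benign tumours never recur, and let b be the benign share of a cohort. The pooled rate is (1 − b) × the rate in malignant patients. For a rate of 10%:

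- b = 10%: 0.9 × 10% = 9.0%
- b = 20%: 0.8 × 10% = 8.0%
- b = 30%: 0.7 × 10% = 7.0%
- b = 40%: 0.6 × 10% = 6.0%

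Two cohorts with identical cancer outcomes and benign shares of 10% and 30% would show 9.0% and 7.0%. The crude apparent hazard ratio is ln(1 − 0.07)/ln(1 − 0.09) = 0.77.

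**Step 3: both together.** With r = d = 10% and b = 30%, Kaplan-Meier shows 7.0% and cumulative incidence 0.7 × 9.5% = 6.65%, against 9.5% in the malignant patients alone. The two effects run in opposite directions, and dilution is the larger unless the benign share is small.

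**The case against.** **The Kaplan-Meier bias is small.** At 10% with 300 patients, the standard error is √(0.1 × 0.9/300) = 1.7 points, so the 95% interval is about ±3.4 points. An excess of 0.25 to 0.5 points is well inside that. This stands, and it limits the importance of the point. It does not remove it: the bias has a known direction, does not shrink with sample size, and is avoided by changing the estimator.

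**Censoring at death is inferred.** The article does not say it. This also stands, but it is the ordinary meaning of Kaplan-Meier for an endpoint that does not include death, and no alternative is named.

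**The population may be settled elsewhere.** A reader might infer that the article places every benign patient in the recurrence denominator. The text does not go that far. The reference to all cohorts can simply mean the four technique groups, and intention to treat concerns cohort assignment. Endpoint populations, log-rank strata and propensity covariates are commonly fixed in the SAP.

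**Adjustment is planned.** A reader might also infer that benign case-mix will surface as differences between techniques. The 9% versus 7% contrast is crude. The plan has a stratified log-rank test and adds a propensity score to the risk models, either of which could account for malignancy. Whether they do cannot be judged, because strata and covariates are not named. The Kaplan-Meier rates themselves carry no stated adjustment, and the three sensitivity analyses cover only the primary endpoints.

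**Cox regression is not at fault.** With deaths censored, it validly estimates a cause-specific hazard.

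**Conclusion.** The point holds in a limited form. The article fixes Kaplan-Meier for two endpoints with a competing event, and the resulting rates would be modestly overstated: by about 0.04 to 1.1 points on assumed 2-year rates of 3–15%, and usually by less than 1 point. Calling the oncologic rates simply wrong would go too far, and Kaplan-Meier is appropriate for overall and disease-free survival.

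The benign-share part is a risk that the text leaves open, not a demonstrated error. Its size depends on a benign share and an imbalance between cohorts for which the article gives no figures.

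Two extensions are tempting but not supported. One is to restrict R0 resection and lymph-node count in the same way: neither is a time-to-event endpoint, so competing risks do not arise, and nodes can be counted in any specimen. The other is to adjust the Cox models for pathological stage: nodal stage depends on the number of nodes harvested, itself a study outcome, so that adjustment could bias the comparison of techniques.

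Only secondary endpoints are involved. The 30-day primary endpoint and the sample size, which is based on it, are unaffected.

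**What to change.** - Estimate local recurrence and metastasis by cumulative incidence functions, with death without the event as a competing event, in patients with histologically confirmed malignancy.
- Keep Kaplan-Meier for overall and disease-free survival. Report disease-free survival in malignant patients, and overall survival both in the whole cohort and in that set.
- State that the Cox models for local recurrence and metastasis are cause-specific.

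If the SAP already says this, it is enough to bring the article's description into line with it.

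The change is one of wording. Pathology is already collected under Table 1, so no new data are needed. Whether the tumour is malignant is settled before the operation even though it is confirmed afterwards, so restricting on it does not condition on an effect of technique. The cost is smaller denominators, and therefore wider intervals, for the secondary oncologic endpoints.

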### Study setting

This will be an international, multicenter study that will take place over a 4-year period, including 2 years of follow-up. The centers chosen will be high volume (recommended > 30 minimally-invasive right colectomies per year) and participating centers should ideally have an implemented enhanced recovery after surgery protocol. All investigators will be qualified colorectal or general surgeons experienced in the surgical management of patients with colon lesions and who have a patient population fitting the study requirements. Surgeons must select one cohort which is understood that is their standard approach. Surgeons will have had completed ≥30 minimally-invasive right colectomy procedures for a colon tumor using their chosen technique, have published their experience or contributed videos for review by the principal investigator and submit pictures of the surgical field when a D3 Lymphadenectomy is performed during the study, and will contribute and consecutively maintain their technique on all eligible subjects during the enrolment phase. Surgeons meeting mentioned criteria will be selected by their technique in order to balance the inclusion of 300 patients in each arm. Different surgeons from the same institution may select different techniques. Surgeons will be able to include patients in any cohort of the study for which they are qualified, and will be asked to enrol at least 15 cases per chosen cohort, per year. It is estimated that each surgeon will include 30 patients in one of the cohorts of the study. This means that we estimate to include 40 surgeons from different centres in Geographical Europe. The number of participating centres will also be close to 40 as in most of the centres only one experienced surgeon will participate in the study. It is desirable that participating centers have an implemented Enhanced Recovery After Surgery (ERAS) protocol although perioperative management including ERAS protocol is difficult to standardize in all multicenter studies.

A screening log with all right colectomies excluded from the study will be kept at all institutions and uploaded to the eCRF.

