### Sample size calculation

The assumptions for the sample size of this study have been developed based on the incidence of Surgical Wound Infection, as well as the incidence of Clavien-Dindo grade > III complications as seen in the Introduction. The sample size is based on attaining a success rate of 85% for the primary endpoint, with the lower 95% confidence limit being no greater than 5% from the estimated success rate. Assuming a 2-sided interval, a total of 245–317 subjects will be required within each cohort. Accounting for a 10% loss to follow up, a total of 1200 subjects will be recruited for this study. Several interim analysis are planned through the study in order to build new power analysis and adjust sample size accordingly if needed.

The design of this study envisages four parallel cohorts for which the sample size has been developed for each cohort according to a precision around an expected success rate with enough subject and sufficient power to make multiple comparisons within the appropriate method. Any statistical inferences drawn based on pairwise comparisons will be undertaken in a posteriori statistical analysis using a propensity score to account for confounding covariates.

The primary endpoint for success is defined as a patient meeting the following criteria:
Surgical Wound Infection 5% lower in the ICA group.Grade IIIb-IV Clavien -Dindo complications at 30 days post op 5% lower in the ICA group.

According to the current literature the the following numbers represent Surgical Wound Infection and Severe Complications in intermediate volume centers:

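### Technique is set mainly by surgeon, yet the precision calculation states no allowance for clustering, and the intervals, unadjusted tests and Cox models are specified at patient level

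*Protocol article*

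**What the plan says.** Study setting (Protocol article) has each surgeon choose the one cohort that represents their standard approach: "It is estimated that each surgeon will include 30 patients in one of the cohorts of the study". Surgeons are selected by technique "in order to balance the inclusion of 300 patients in each arm", and 40 surgeons in about 40 centres are expected, most centres supplying one surgeon. The same section lets surgeons at one institution choose different techniques, and also lets a surgeon enrol in any cohort for which they are qualified.

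Sample size calculation fixes each cohort by precision. It takes 85% success as given and asks for an interval "with the lower 95% confidence limit being no greater than 5% from the estimated success rate". The resulting requirement is put this way: "Assuming a 2-sided interval, a total of 245–317 subjects will be required within each cohort". The recruitment target then adds attrition: "Accounting for a 10% loss to follow up, a total of 1200 subjects will be recruited for this study". Pairwise inference is assigned to a later propensity-score analysis.

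Statistical analysis provides proportions with 95% confidence intervals per cohort. It then says "Exploratory comparisons of discrete variables will be performed using a Chi-squared test" (continuity-corrected, or Fisher's exact test) and adds t or Wilcoxon tests, a stratified log-rank test and Cox regression. One two-sided 0.05 threshold covers all tests. On clustering, it notes that the generalized linear model approach permits multilevel and mixed models, "which will be useful for controlling the inter-hospital random variability".

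**The concern.** Patients of one surgeon share that surgeon's skill, case mix and perioperative habits, so their outcomes are likely to be correlated. When technique is also constant within surgeon, that correlation goes straight into the variance of every contrast between techniques. A technique comparison then rests on about 10 surgeons against 10, and not on 300 independent patients against 300. Methods that treat patients as independent give intervals that are too narrow and p-values that are too small at any positive ICC.

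Comparing the four techniques is the purpose of the study. A reader of the results would see per-cohort rates with intervals, and tests judged at 0.05, and would take both at face value. The stated 5-point precision is exposed in the same way, because no clustering allowance is stated in it.

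**Working it through.** **Inputs from the protocol.** Success rate p = 0.85; distance to the lower limit d = 0.05; two-sided 95% interval; 300 per cohort; 10% loss, so 300 × 0.9 = 270 evaluable; 30 patients per surgeon, so 300/30 = 10 surgeons per cohort and 30 × 0.9 = 27 evaluable each.

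**Assumed input.** The ICC is not in the document; 0.01, 0.02 and 0.05 are used as a range.

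**The plan's own figure, with independent patients.**
- Wald: n = 1.96² × 0.85 × 0.15 / 0.05² = 195.9, so 196.
- Wald with continuity correction: 216. Wilson lower limit: 246. Exact lower limit: 254.
- The lower end, 245, is therefore reproduced within one patient by Wilson, with no clustering.
- The upper end, 317, does not follow from the stated inputs. Several unstated ones come close: Wald at alpha 0.05/4 gives 319, 80% power at one-sided 0.05 gives 316, and 246 × 1.29 (ICC 0.01, 30 per surgeon) gives 317. The figure is no evidence that clustering was, or was not, considered.
- With 10% loss, 245/0.9 gives 273 and 317/0.9 gives 353. Recruiting 300 covers the lower end only.

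**Adding clustering.** Design effect DE = 1 + (27 − 1) × ICC. Half-width = 1.96 × √(0.85 × 0.15 × DE / 270). Effective n = 270/DE. Approximate type I error of the naive two-cohort test = 2 × (1 − Φ(1.96/√DE)); coverage of the naive interval is 1 minus the same quantity. Both were also simulated with beta-binomial data: 10 surgeons × 27 patients per cohort, event rate 15%, technique constant within surgeon, 40,000 runs.

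| Assumed ICC | DE | Effective n | Half-width (points) | Coverage, formula / simulated | Chi-squared type I error, formula / simulated | With continuity correction, simulated |
|---|---|---|---|---|---|---|
| 0 | 1.00 | 270 | 4.3 | 95% / – | 5% / 4.9% | – |
| 0.01 | 1.26 | 214 | 4.8 | 91.9% / 91% | 8.1% / 8.0% | 6.5% |
| 0.02 | 1.52 | 178 | 5.3 | 88.8% / 88% | 11.2% / 11.3% | 9.4% |
| 0.05 | 2.30 | 117 | 6.5 | 80.4% / 80% | 19.6% / 19.1% | 16.7% |

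**Where the 5-point target fails.** By the Wald formula, 270 evaluable patients tolerate DE = 270/195.9 = 1.378, so ICC = 0.378/26 = 0.0145. With all 300 evaluable (30 per surgeon) the limit is (300/196 − 1)/29 = 0.018. Measured against the protocol's own minimum of 245, the tolerance is DE = 270/245 = 1.10, so ICC = 0.102/26 = 0.004.

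**Sensitivity to cluster size.** With 30 evaluable per surgeon, the half-widths are 4.6/5.1/6.3 points and the simulated type I errors 8.4/12.0/21.2%.

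**The case against.** The strongest reply is that the plan does not rest its conclusions on the plain chi-squared test. That test is labelled exploratory, pairwise inference is given to propensity-adjusted models, and multilevel models for hospital variability are mentioned. Since most centres supply one surgeon, a hospital random effect would absorb most surgeon clustering. There is also a leave-one-hospital-out sensitivity analysis, and a separate analysis plan may hold the details.

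Much of this stands. A reader might infer that the study's main adjusted comparisons carry an 8–19% false-positive rate. The document does not support that: the figures belong to the unadjusted, uncorrected chi-squared test, and no inflation is shown for a mixed model that contains the cluster. They also assume full nesting of technique in surgeon, whereas Study setting has one statement that a surgeon selects a single cohort and another allowing enrolment in any cohort for which the surgeon is qualified. A reader might also infer that the precision target is certainly missed. It is not: at ICC 0.01 the Wald half-width is still 4.8 points, and the plan foresees interim re-assessment of sample size.

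Some of it does not answer the point. The multilevel sentence describes what the model class can do, and does not say that such a model will be fitted. It concerns generalized linear models, so it leaves out the per-cohort intervals, the log-rank test and Cox regression. Where two surgeons at one hospital use different techniques, a hospital effect does not capture the difference between them. Propensity adjustment on patient covariates addresses confounding and does not correct standard errors for clustering. Leaving out one hospital at a time shows influence and does not correct the variance. The exploratory label is attached to discrete comparisons, while the 0.05 threshold covers all tests.

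**Conclusion.** The point holds in a limited form. As written, the protocol states no clustering allowance in its precision calculation. It specifies patient-level intervals, unadjusted tests and Cox models for a design in which technique is set mainly by about 10 surgeons per cohort. The direction of the error is certain for any positive ICC, but its size depends on a value that the document does not give. Over the assumed range 0.01–0.05, the half-width runs from 4.8 to 6.5 points and coverage of the nominal 95% interval from about 91% to 80%. Under full nesting, type I error of the unadjusted chi-squared test runs from about 8% to 19%. The 5-point target is met at 0.01 and fails above about 0.015 with 270 evaluable patients. No size was computed for the log-rank or Cox analyses.

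A reader might further infer that a cluster term would stop surgeon skill from being read as a technique effect. It would not. Random effects or robust errors correct the variance, and where technique is constant within surgeon the two remain confounded.

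**What to change.** - Commit, in place of the permissive sentence, to a surgeon random intercept (nested in hospital where a hospital has several surgeons), or to surgeon-clustered robust errors. Either needs a small-sample correction, given about 10 surgeons per cohort. Apply it to every between-technique comparison and every per-cohort interval.
- Use a shared frailty or a clustered sandwich variance for the Cox models.
- Treat the unadjusted chi-squared/Fisher, t/Wilcoxon and log-rank results as descriptive.
- Restate the precision over a declared ICC range such as 0.01–0.05, and show the inputs behind 245–317.
- Reconcile the two statements in Study setting on whether a surgeon may contribute to more than one cohort.
- State the confounding of surgeon skill with technique as a limitation.

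The cost is wording in the protocol and analysis plan, plus a surgeon identifier in the analysis file. The downside is wider intervals and a less favourable stated precision.

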**Table Taba:** 

ICA		ECA
Surgical Wound Infection	_4–5%_^5,8,10^	_10–14%_^5,8,10^
Morbidity Dindo 3b-4	1.1–5%^5,8^	8–11%^5,8^

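### The interim rule excludes a cohort from further analysis on its own primary outcome, a material risk that falls almost only on the extracorporeal (ECA) cohorts

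*Protocol article*

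**What the plan says.** The Statistical analysis section of the protocol article sets the look: "An interim analysis is planned after having recruited 300 patients, 75 patients at least per cohort". Its purpose is given as "in order to evaluate whether a success rate around 85% is achieved for each cohort". The section then says "a lower limit of 75% is not acceptable", and gives the consequence: "the data from the treatment groups with a success rate < 75% will be excluded from further analysis". Earlier in the same section, the cohorts are to be analysed by intention to treat.

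Under Outcomes, a patient with either a surgical wound infection or a Clavien-Dindo IIIb–IV complication counts as a failure. The table after Sample size calculation gives the literature rates for the two components. For ECA these are 10–14% for wound infection and 8–11% for the row "Morbidity Dindo 3b-4"; for ICA they are 4–5% and 1.1–5%. The text introduces them with the words "numbers represent Surgical Wound Infection and Severe Complications in intermediate volume centers".

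Sample size calculation also says: "Several interim analysis are planned through the study in order to build new power analysis and adjust sample size accordingly if needed".

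**The concern.** The rule decides which cohorts are analysed by looking at the outcome the study is meant to estimate. A cohort that does badly in its first 75 or so patients leaves the analysis, and one that does well stays. That is hard to square with intention to treat, under which patients are analysed in their cohort whatever their result.

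The Background gives the comparison of ICA with ECA, under both laparoscopic and robotic surgery, as the purpose of the study. Losing one ECA cohort removes two contrasts: ICA against ECA within that surgical approach, and robot against laparoscopy within ECA. If ECA does have more failures, as the literature table suggests, the rule acts against the evidence that would show it. An ECA cohort that survives the look has been selected for a good early result, so its estimate is biased upward.

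The 75% floor also lies at the lower edge of what the article's own figures imply for ECA, so the trigger is not remote.

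**Working it through.** The article gives no operating characteristics for this rule, so there is no stated figure to reproduce.

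**Inputs.** 75 patients per cohort (300 in total with at least 75 in each of four cohorts, and 4 × 75 = 300) and a cut-off of 75%, both from Statistical analysis. Wound infection rate *a* and grade IIIb–IV rate *b*, from the literature table. The overlap of the two events within a patient is not given, so it is an assumption, taken over its range.

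**Step 1: true success.** No overlap: 1 − a − b. Independence: (1 − a)(1 − b). Full overlap: 1 − max(a, b). For example, at the top of the ECA range, 1 − 0.14 − 0.11 = 75.0%, 0.86 × 0.89 = 76.5%, and 1 − 0.14 = 86%.

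**Step 2: exclusion.** 0.75 × 75 = 56.25, so a cohort is excluded with 56 or fewer successes. The probability is q = P(X ≤ 56) for X ~ Binomial(75, p). For two independent ECA cohorts, at least one is excluded with probability 1 − (1 − q)² and both with q².

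| ECA rates (a, b) | Overlap | True success | One cohort (q) | At least one of two | Both |
|---|---|---|---|---|---|
| Low: 10%, 8% | none | 82.0% | 7.1% | 14% | 0.5% |
| | independent | 82.8% | 4.8% | 9% | 0.2% |
| | full | 90% | 0.01% | 0.02% | about 0 |
| Midpoint: 12%, 9.5% | none | 78.5% | 24.8% | 43% | 6.1% |
| | independent | 79.6% | 17.6% | 32% | 3.1% |
| | full | 88% | 0.1% | 0.2% | about 0 |
| High: 14%, 11% | none | 75.0% | 51.8% | 77% | 26.8% |
| | independent | 76.5% | 39.4% | 63% | 15.5% |
| | full | 86% | 0.65% | 1.3% | about 0 |

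The chance of losing at least one ECA cohort passes 50% once true ECA success is about 77.5% or lower.

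**Step 3: the other cohorts.** The ICA rates imply 90–96% success, for which q is at most 0.01%. A cohort truly at the planned 85% has q = 1.3%.

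**Step 4: sensitivity to the count.** With 80 patients per cohort the 4.8–51.8% range becomes 2.7–44.0%, and with 100 it becomes 1.7–44.7%.

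**Step 5: bias in survivors.** At a true 76.5%, an ECA cohort that passes the look shows 79.7% on average at the interim. If 225 further patients bring it to 300, the expected final figure is (75 × 0.797 + 225 × 0.765)/300 = 77.3%, about 0.8 points too high.

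**Step 6: the other reading of the floor.** If the lower limit means a lower 95% confidence limit, a cohort needs 63 (Wald) or 64 (exact) successes out of 75. A cohort truly at 85% would then fail with probability 33% or 45%, against 1.3% when the observed rate is used.

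**The case against.** The strongest reply is that the 75% figure is an acceptability floor for a technique, and that its trigger probability depends on assumptions. Much of this stands.

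- A reader might infer that exclusion of ECA is likely. The documents do not support that. The literature rates never put ECA success below 75%, and the chance for a single cohort reaches one half only at the worst corner of the range. The rates come from intermediate-volume centres, whereas Study setting selects high-volume centres and experienced surgeons, so true ECA success may be higher.
- A reader might infer that the rule removes the ECA comparator altogether. That requires both ECA cohorts to fail. If one fails, ICA against ECA can still be compared within the other surgical approach.
- A reader might infer that data are deleted or the poor result hidden. The text speaks of exclusion from further analysis. It does not say that records are removed or that the interim result goes unreported.
- A reader might infer that the interim looks inflate type I error. Sample size calculation does not say which quantities would drive a change in size, so this cannot be shown from the article.
- The operative clause refers to the success rate, so the confidence-limit figures in step 6 show why the wording matters. They do not measure the main rule.

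None of this removes the defect. The exclusion is stated outright as current text, so it is not a detail left to the SAP. Outcome-dependent removal of a cohort is unsound whatever its probability.

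**Conclusion.** The point holds as a material risk that depends on assumptions. Over the article's own ECA rates, from independent events to no overlap, the chance of exclusion is 5–52% per ECA cohort, 9–77% for at least one (32–43% at the midpoint) and at most 27% for both. With full overlap it is under 1% per cohort. ICA cohorts are practically never affected, so the rule bears almost only on one side of the main comparison. The upward bias in a surviving ECA cohort is about 3 points at the interim and under 1 point at 300 patients for a true 76.5%. The larger harm is the loss of contrasts.

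These figures assume that the literature rates apply, that there are 75 evaluable patients per cohort, that patients and cohorts are independent, and that the observed rate is what is compared with 75%. The clause should be changed before any interim look, because one sentence can remove part of the comparison the study was designed to make.

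**What to change.** In Statistical analysis, remove the exclusion clause and put in its place: *All four cohorts remain in every planned analysis and in the study report, whatever their success rate at the interim look.* The 75% floor may stay as a descriptive benchmark, with a statement of whether it refers to the observed rate or to a confidence limit.

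Reconcile the single interim analysis described there with the several mentioned under Sample size calculation, giving the number and purpose of the looks. Carry the same wording into the SAP.

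The cost is wording only, with no extra patients or data. The downside is that the sponsor gives up the option to drop a poorly performing cohort's data from the analysis.
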